#### Table 2 Primary and secondary objectives and research questions

1. **Primary objective and research question**

| **Objective:** | To compare overall survival (OS) in patients > 18 years with metastatic [organ]carcinoma with a biomarker Y+ mutation who have shown progression after first line treatment and have indicated informed consent for longitudinal observational data collection as part of the XYZ Registry and are treated with a combination of Drug A and Drug B compared to controls who are treated with standard care for a period of a maximum of 2 years (or 4 years). Comparator patients will be included retrospectively as well prospectively. |
| --- | --- |
| **Hypothesis:** | Overall survival will be improved with Drug A and Drug B compared to standard of care. |
| **Population *(mention key inclusion-exclusion criteria):*** | Patients with biomarker Y+ positive metastatic [organ] cancer who progressed after at least of one line of treatment |
| **Exposure:** | Initiation of Drug A in combination with Drug B |
| **Comparator:** | Standard of care. In [anonymous country], SoC second line therapy is Drug C or in third line the SoC is Drug D. There will be 2 comparator arms. One will be initiation of Drug C or Drug D using concurrent years of data with the exposure arm. The other comparator group will be initiatiors of Drug C or Drug D using historical controls from years of data prior to availability of Drug A/B. |
| **Outcome:** | Overall Survival (OS) |
| **Time *(when follow up begins and ends):*** | Follow up from day after initiation of therapy until the first of outcome, discontinuation, add/switch therapy, disenrollment, end of study period, nursing home admission, death, progression of therapy, others to be discussed. |
| **Setting:** | Outpatient care |
| **Main measure of effect:** | Hazard Ratio (to be discussed). |

1. **Secondary objective 1 and research question**

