#### Table 3 Operational Definition of Time 0 (index date) and other primary time anchors

| **Study population name(s)** | **Time Anchor Description**  **(e.g. time 0)** | **Number of entries** | **Type of entry** | **Washout window** | **Care Setting^1^** | **Code Type^2^** | **Diagnosis position** | **Incident with respect to…** | **Measurement characteristics/**  **validation** | **Source of algorithm** |
| --- | --- | --- | --- | --- | --- | --- | --- | --- | --- | --- |
| **Exposure**  Drug A/B | Date of incident dispensation of Drug A/B (time 0) | Single | Incident | [-∞, 0] | n/a | ATCC | n/a | Drug A or Drug B alone, Drug A/B in combination, Drug D | No validation study | Investigator review of drug codes  XYZ registry dispensing data years 2021-2022 |
| **Comparator 1**  (concurrent)  Standard of Care (SoC).  Drug C or Drug D | Date of incident dispensation of standard care  (time 0) | Single | Incident | [-∞, 0] | n/a | ATCC | n/a | Drug C initiators must be incident with respect to Drug A, B, C and D  Drug D initiators must be incident with respect to Drug A, B, D but not C. | No validation study | Investigator review of drug codes  XYZ registry dispensing data years 2021-2022 |
| **Comparator 2**  (historical)  Standard of Care (SoC).  Drug C or Drug D | Date of incident dispensation of standard care (time 0) | Single | Incident | [-∞, 0] | n/a | ATCC | n/a | Drug C initiators must be incident with respect to Drug A, B, C and D  Drug D initiators must be incident with respect to Drug A, B, D but not C. | No validation study | Investigator review of drug codes  XYZ registry dispensing data years 2019-2020 |

^1^ IP = inpatient, OP = outpatient, ED = emergency department, OT = other, n/a = not applicable

^2^See appendix for listing of clinical codes for each study parameter

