#### 7.4.1 Context and rationale for exposure(s) of interest

Exposure to Drug A/B and standard of care comparators will be defined using ATCC codes. Drug A/B combination is approved for 2^nd^ or 3^rd^ line therapy for metastatic [organ] cancer for biomarker Y+ cancers. Drugs C and D are approved as standard of care for 2^nd^ and 3^rd^ line therapies, respectively.

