#### Table 8. Operational Definitions of Follow Up

|  |  |  |  |
| --- | --- | --- | --- |
| **Follow up start** | Day 1 |  |  |
| **Follow up end^1^** | **Select all that apply** |  | **Specify** |
| **Date of outcome** | Yes |  | See Table 5 |
| **Date of death** | Yes |  | Discharged dead or registry recorded death, whichever came 1st |
| **End of observation in data** | Yes |  | Allow 30 day gaps in enrolment |
| **Day X following index date**  *(specify day)* | Yes |  | Day 365 |
| **End of study period**  (specify date) | Yes |  | 30-Sep-15 |
| **End of exposure**  *(specify operational details,*  *e.g. stockpiling algorithm, grace period)* | Yes |  | **Stockpiling algorithm:** If refill occurs before end of days supply, count overlapping days at the end of the subsequent dispensing’s day supply.  **Grace period:** Bridge gaps of ≤30 days between dispensation + days supply and refill. Add 30 days to last dispensation + days supply in a treatment episode. |
| **Date of add to/switch from exposure**  *(specify algorithm)* | Yes |  | Date that patient in exposed group is dispensed comparator drug or vice versa |
| **Other date** *(specify)* | Yes |  | Nursing home admission |

^1^ Follow up ends at the first occurrence of any of the selected criteria that end follow up.

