#### 7.4.4 Context and rationale for covariates (confounding variables and effect modifiers, e.g. risk factors, comorbidities, comedications)

We will adjust for major confounders such as age and sex. In the primary analysis, we will balance the Drug A/B exposed group (2^nd^ or 3^rd^ line) and Drug C (2^nd^ line) or D (3^rd^ line) SoC comparator group on prior exposure to Drug C, which will be an indicator of line of therapy. Patients who initiate Drug A/B and have prior exposure to Drug C are assumed to be 3rd line therapy. Those without prior exposure to Drug C are assumed to be on 2^nd^ line therapy. SoC initiators of Drug C (2nd line) will not have prior exposure because of the washout imposed to define new initiation and will be considered on 2^nd^ line therapy, in accordance with guidelines for use. SoC initiators of Drug D will be considered on 3rd line therapy regardless of whether they had prior exposure to Drug C (2^nd^ line therapy). Other covariates are to be determined after additional discussion.

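### The Table 8 switch rule censors a move to Drug D in the A/B arm but not in the Drug C part of the comparator, and it conflicts with Table 2 and section 7.1

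*Protocol*

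**What the plan says.** The primary contrast is A/B against one concurrent comparator arm. Table 2 describes that arm as "One will be initiation of Drug C or Drug D using concurrent years of data with the exposure arm". The same table places the two drugs in sequence: "SoC second line therapy is Drug C or in third line the SoC is Drug D". Moving from C to D is therefore the ordinary next step for a second-line comparator patient. A/B patients can be second line too. Section 7.4.4 says of them: "Those without prior exposure to Drug C are assumed to be on 2^nd^ line therapy". Table 3 allows one entry per patient, so a Drug C patient who later receives Drug D does not re-enter as a Drug D initiator.

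Three parts of the protocol say when follow-up ends:

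- **Table 8, switch row:** "Date that patient in exposed group is dispensed comparator drug or vice versa". Only crossings between the exposed and comparator groups are named.
- **Table 8, end-of-exposure row:** "Add 30 days to last dispensation + days supply in a treatment episode". It does not say whether an episode is one of the index drug or of the pooled standard of care. The footnote adds: "Follow up ends at the first occurrence of any of the selected criteria that end follow up". Table 8 has no row for progression.
- **Table 2 and section 7.1:** Table 2 stops follow-up at discontinuation, at any added or switched therapy and at progression, with no limit to crossings between groups. Section 7.1 lists progression and treatment failure as censoring events.

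Section 7.4.3 specifies an on-treatment analysis for death but refers the reader to Table 6 for the censoring rules. They are in Table 8.

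**The concern.** The same event, a move from a second-line drug to Drug D, is handled differently by arm. In the A/B arm it ends follow-up on the day of dispensing. In the Drug C part of the comparator the switch row does not apply. Such a move will often follow progression, when the risk of death is plausibly higher. Some or all of that later, higher-risk time and its deaths would then count for standard of care but not for A/B.

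The outcome is the primary one, and the Cox model in Table 10 contains exposure only. Balancing on line of therapy works at baseline and cannot correct a difference that arises after time 0 within second-line pairs. The risk is a hazard ratio below 1 with no treatment effect, of a size comparable with the effect the study is powered to find.

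**Working it through.** **1. The plan's own figure.** Inputs from section 7.9: about 5,000 exposed, 1:1 matching, 35% deaths at one year, HR 0.90. Two-sided 5% is implied by the 95% interval in Table 10. Schoenfeld: power = Φ(|ln HR|·√(d/4) − 1.96).

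- 35% in both arms: d = 10,000 × 0.35 = 3,500. 0.1054 × √875 = 3.117, and Φ(1.157) = 87.6%.
- 35% in standard of care with HR 0.90 on A/B: d = 3,357, giving 86.3%.

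The stated power above 80% is reproduced, so 0.90 is a fair yardstick for the bias.

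**2. Who is censored when Drug D is dispensed.**

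| Text applied | A/B to D | C to D |
|---|---|---|
| Table 8 switch row | Censored that day | Not a switch |
| Table 8, end of exposure for pooled group | Censored that day | Followed through Drug D |
| Table 8, end of exposure per drug | Censored that day | Followed to last Drug C supply + 30 days |
| Table 2, section 7.1 | Censored at or before the move | Censored at or before the move |

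Both readings of Table 8 are unequal between arms. Table 2 and section 7.1 are not. For the historical comparator, taken from years before A/B was available, the reverse limb of the switch row cannot operate at all.

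**3. Size of the bias with no true effect.** The protocol gives no switching rate and no hazard after the move, so these are assumptions shown as ranges. Three-state model, same in both arms, all patients second line, follow-up capped at 365 days:

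- h = death hazard before the move; k·h = hazard after it, with k from 0.5 to 3.
- s = −ln(1 − p) = rate of moving, where p is the one-year probability of moving in the absence of death, 20%, 40% or 60%.
- h is solved from 1 − e^(−(h+s)) − s[e^(−kh) − e^(−(h+s))]/(h + s − kh) = 0.35.

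Worked case, k = 2 and p = 40%: s = 0.511 and h = 0.359. Check: 1 − 0.419 − 0.511 × (0.488 − 0.419)/(0.870 − 0.718) ≈ 0.35. An A/B patient censored at the move contributes deaths at rate 0.359. A Drug C patient followed through D contributes 0.35 deaths over 0.821 person-years, a rate of 0.426. The ratio is 0.359/0.426 = 0.84. The Cox HR from simulation (400,000 per arm) is 0.85.

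Simulated HR for A/B against standard of care, for 20/40/60% moving to D:

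| Handling of C to D | k = 0.5 | k = 1 | k = 1.5 | k = 2 | k = 3 |
|---|---|---|---|---|---|
| Followed through D | 1.05/1.12/1.19 | about 1.00 | 0.96/0.92/0.88 | 0.91/0.85/0.78 | 0.87/0.75/0.65 |
| Followed 30 days past the move | 1.01/1.03/1.04 | about 1.00 | 1.00/0.98/0.97 | 0.97/0.97/0.94 | 0.97/0.93/0.88 |
| Censored at the move (symmetric) | about 1.00 | about 1.00 | about 1.00 | about 1.00 | about 1.00 |

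Simulation noise is about 0.01. At k = 2 and 20% the shared A/B sample ran low (symmetric HR 0.988). Dividing by it gives 0.914/0.988 = 0.93 and 0.973/0.988 = 0.98. Repeat runs put these two cells at 0.91–0.93 and 0.97–0.99, so the ranges at k = 2 are about 0.93–0.78 and 0.99–0.94.

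**4. Dilution.** If half of the Drug C patients who move go to A/B, and so are censored, the first row at k = 2 becomes 0.95/0.91/0.85. Third-line pairs have no C-to-D step, so they also pull the HR towards 1.

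**The case against.** A reader might infer that the plan certainly follows Drug C patients to day 365 on Drug D and so creates a false survival benefit. The documents do not support that. The first criterion met ends follow-up, and the exposure algorithm in section 7.4.1 is written in terms of refills. A Drug D dispensing is not naturally a refill of Drug C, so the per-drug reading is at least as natural, and it shrinks the bias considerably. Table 2 and section 7.1 would remove it. This part of the objection stands: the defect is an unequal row within an unreconciled set of rules, not one settled rule.

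A reader might also reach for an extreme figure. A null HR as low as 0.39 can be simulated, but it needs the pooled reading, all patients second line and the harshest assumed progression, hazard and switching rates. None of these is in the protocol.

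The direction is conditional too: no bias if the hazard is unchanged after the move, and reversal if it falls.

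Finally, the protocol is a first version, leaves further follow-up criteria open, acknowledges informative censoring in section 8 and plans censoring weights. But the Table 8 switch row is filled in, not marked for discussion, and would be programmed as written. The weights are sensitivity analyses and leave the primary estimate unchanged.

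**Conclusion.** The point holds in conditional form. As written, the Table 8 switch row treats the same move differently by arm, the end-of-exposure row does not restore symmetry on either reading, and both disagree with Table 2 and section 7.1. If the death hazard doubles after the move and 20–60% of patients move, the null HR is about 0.93–0.78 on the pooled reading and about 0.99–0.94 on the per-drug reading. On the pooled reading, with a doubled hazard and 40% or more moving, the spurious effect exceeds the design effect of 0.90. On the per-drug reading at a doubled hazard it stays smaller than the design effect.

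These sizes rest on assumed switching and hazard ranges, equal switching in both arms and an all-second-line population. They are not predictions for this registry.

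**What to change.** For the on-treatment analysis:

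1. Reword the Table 8 switch row so that, in every arm, follow-up ends at the first dispensing of any anticancer drug other than the index drug. C to D then counts as a switch.
2. State in the end-of-exposure row that the treatment episode is that of the index drug, not of the pooled standard of care.
3. Reconcile Table 8 with Table 2 and section 7.1, including whether progression ends follow-up for overall survival, and apply the answer to all arms.
4. Correct the cross-reference in section 7.4.3 from Table 6 to Table 8.

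The cost is a few sentences. The standard-of-care arm loses some person-time and deaths, so the expected number of events should be looked at again. Informative censoring within each arm remains and should be examined with the censoring-weight analyses already planned. Not censoring overall survival at a drug change would also treat the arms alike, but it replaces the on-treatment estimand and is a separate decision.

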#### 7.4.4 Context and rationale for covariates (confounding variables and effect modifiers, e.g. risk factors, comorbidities, comedications)

We will adjust for major confounders such as age and sex. In the primary analysis, we will balance the Drug A/B exposed group (2^nd^ or 3^rd^ line) and Drug C (2^nd^ line) or D (3^rd^ line) SoC comparator group on prior exposure to Drug C, which will be an indicator of line of therapy. Patients who initiate Drug A/B and have prior exposure to Drug C are assumed to be 3rd line therapy. Those without prior exposure to Drug C are assumed to be on 2^nd^ line therapy. SoC initiators of Drug C (2nd line) will not have prior exposure because of the washout imposed to define new initiation and will be considered on 2^nd^ line therapy, in accordance with guidelines for use. SoC initiators of Drug D will be considered on 3rd line therapy regardless of whether they had prior exposure to Drug C (2^nd^ line therapy). Other covariates are to be determined after additional discussion.

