#### Table 9. Operational Definitions of Covariates

| **Characteristic** | **Details** | **Type of variable** | **Assessment window** | **Care Settings¹** | **Code Type^2^** | **Diagnosis Position^3^** | **Applied to study populations:** | **Measurement characteristics/validation** | **Source for algorithm** |
| --- | --- | --- | --- | --- | --- | --- | --- | --- | --- |
| Age | (cohort entry year - year of birth) | Continuous | [0,0] | n/a | n/a | n/a | Exposure, comparator 1, comparator 2 | n/a | n/a |
| Sex | Male, Female | Categorical | [0, 0] | n/a | n/a | n/a | Exposure, comparator 1, comparator 2 | n/a | n/a |
| 2^nd^ vs 3^rd^ line therapy | If Drug A/B initiator and prior exposure to Drug C 🡪 3^rd^ line, otherwise 2^nd^ line  If Drug C initiator 🡪 2^nd^ line  If Drug D initiator 🡪 3^rd^ line | Binary | [-∞, 0] | *n/a* | *n/a* | *n/a* | Exposure, comparator 1, comparator 2 | No validation study | n/a |
| To be added |  |  |  |  |  |  |  |  |  |

^1^ IP = inpatient, OP = outpatient, ED = emergency department, OT = other, n/a = not applicable

^2^ See appendix for listing of clinical codes for each study parameter

^3^ Specify whether a diagnosis code is required to be in the primary position (main reason for encounter)

- 1. Data analysis

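### Line of therapy is coded from prior Drug C for A/B initiators but from the drug started for Drug D initiators, so the line subgroups, and the primary HR if Table 9 feeds the propensity score, rest on a code that differs by arm

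*Protocol*

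**What the plan says.** Section 7.4.4 of the protocol names the variable to be balanced in the primary analysis, for the A/B group and the "SoC comparator group on prior exposure to Drug C, which will be an indicator of line of therapy".

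The coding rules that follow differ by arm:

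- A/B initiators are coded from history. "Patients who initiate Drug A/B and have prior exposure to Drug C are assumed to be 3rd line therapy", and "Those without prior exposure to Drug C are assumed to be on 2^nd^ line therapy".
- Drug C initiators are 2nd line, because the washout excludes earlier Drug C.
- Drug D initiators are coded from the drug started: "SoC initiators of Drug D will be considered on 3rd line therapy regardless of whether they had prior exposure to Drug C".

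Table 9 makes this operational. The A/B condition begins "If Drug A/B initiator and prior exposure to Drug C"; the Drug D condition is only "If Drug D initiator", with no reference to history.

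Table 3 sets the entry rule for both comparator groups: "Drug D initiators must be incident with respect to Drug A, B, D but not C". Prior Drug C is thus permitted but not required. Table 10 lists 2nd versus 3rd line as the only subgroup, for overall survival and for progression-free survival.

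**The concern.** A covariate used to make the arms comparable should be derived in the same way in both, from information that precedes treatment choice. Here one cell breaks that rule. A patient with no recorded Drug C is 2nd line if A/B is started and 3rd line if Drug D is started. For that patient, the variable section 7.4.4 says it will balance (prior Drug C: no) and the Table 9 variable (3rd line) point in opposite directions, and a programmer cannot follow both.

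The 3rd-line subgroup would compare A/B patients who all had Drug C with Drug D patients some of whom had not. If the Table 9 variable also goes into the propensity score, the same unlike comparison enters the primary HR. The design is powered for an HR of 0.90, so moderate miscoding could remove a good part of the effect sought.

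**Working it through.** **1. Codes side by side**

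| Drug started | Prior Drug C recorded | Variable named for balancing in 7.4.4 | Line in Table 9 |
|---|---|---|---|
| A/B | yes | yes | 3rd |
| A/B | no | no | 2nd |
| Drug C | no (washout) | no | 2nd |
| Drug D | yes | yes | 3rd |
| Drug D | no | no | **3rd** |

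Only the last row departs from the history rule. Table 3 admits these patients, and the wording of 7.4.4 shows that they are expected.

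**2. What follows under each variable**

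- *Table 9 line in the propensity score.* Drug D patients without Drug C count as 3rd line and can be paired with A/B patients who had Drug C. The primary HR and the 3rd-line subgroup are both affected.
- *Prior Drug C in the propensity score, taken literally.* Drug D patients without Drug C are comparable on this variable with A/B patients without Drug C. If Drug C records are complete, the primary HR avoids the unlike pairing. The subgroups do not: Table 9 puts such a pair's A/B member in the 2nd-line subgroup and its Drug D member in the 3rd-line subgroup.

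**3. The plan's own power figure**

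The study size section gives 5,000 exposed, 1:1 matching, 35% deaths in 1 year and HR 0.90. Two-sided alpha of 0.05 is inferred from the 95% interval in Table 10.

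Events = 10,000 × 0.35 = 3,500.
Power = Φ(√3,500/2 × |ln 0.90| − 1.96) = Φ(3.117 − 1.960) = 87.6%.

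This agrees with the stated figure of more than 80%. The power statement is not in error on this point.

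**4. Illustration of size**

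These assumptions are not in the documents:

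- true HR 0.90 in both lines (the protocol gives 0.90 only as a detectable effect);
- 2nd-line SoC hazard −ln(0.65) = 0.4308 per year, that is, the 35% one-year figure assigned to 2nd line;
- 3rd-line hazard r times the 2nd-line hazard;
- a share p of Drug D initiators truly 2nd line;
- half of the pairs coded 3rd line;
- exponential survival, censored at 1 year.

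Approximate formulas, as ratios of mean hazards:

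- 3rd-line stratum: HR ≈ 0.90 / (1 − p + p/r)
- overall: HR ≈ 0.90 × (1 + r) / (1 + r(1 − p) + p)

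For r = 1.5 and p = 20%, the stratum gives 0.90/0.9333 = 0.964 and the overall HR is 0.90 × 2.5/2.4 = 0.938. Solving for the limiting Cox HR numerically gives:

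| r | p | HR, 3rd-line stratum | HR, overall | Power for overall HR at 3,500 events |
|---|---|---|---|---|
| 1.25 | 10% | 0.919 | 0.910 | 79% |
| 1.25 | 20% | 0.939 | 0.921 | 69% |
| 1.25 | 30% | 0.960 | 0.931 | 56% |
| 1.5 | 10% | 0.934 | 0.919 | 70% |
| 1.5 | 20% | 0.970 | 0.938 | 47% |
| 1.5 | 30% | 1.008 | 0.958 | 25% |
| 2.0 | 10% | 0.957 | 0.934 | 52% |
| 2.0 | 20% | 1.018 | 0.968 | 16% |
| 2.0 | 30% | 1.085 | 1.002 | none |

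At p = 0 the stratum HR is 0.900, and the overall HR is 0.900 to 0.903 with power of 86% to 88%. The overall and power columns apply only if the Table 9 variable is used for matching.

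**5. If the drug label is right and the Drug C record is wrong**

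Suppose Drug D initiators really are 3rd line and some Drug C use went unrecorded. The same gaps would affect A/B patients, but Table 9 overrides the record only for Drug D. With half of the A/B patients truly 3rd line, 10% of Drug C use unrecorded and r = 1.5, the 2nd-line subgroup HR is 0.938 and the overall HR 0.919, against a true 0.90.

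**The case against.** The best defence is that the Drug D rule is a deliberate and disclosed proxy. Section 7.4.1 states that "Drugs C and D are approved as standard of care for 2^nd^ and 3^rd^ line therapies, respectively". A Drug D starter with no Drug C record may have had a different or unrecorded second-line drug, and the label would then measure line better than the record. This stands to the extent that the documents do not show such patients had first-line therapy only. It does not explain why the record is overridden in one arm and trusted in the other.

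A reader might infer that the primary HR is certain to be biased. The documents do not support that. Section 7.4.4 names prior Drug C as the variable to balance; if that is what enters the propensity score and the records are complete, the primary HR can escape. What is certain is the conflict between the two variables and the arm-dependent coding of the subgroups.

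The direction is also conditional. It needs later line to carry worse survival and Drug D starters who skipped Drug C to be otherwise comparable. If Drug C was skipped for reasons tied to poor prognosis, the direction could reverse.

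Finally, the protocol is a draft and other covariates are still to be determined. The line rule, however, is written out in full in both the text and Table 9, so it is not one of the deferred items.

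**Conclusion.** The point holds as an internal conflict with a definite consequence for the subgroups and a conditional one for the primary analysis. For Drug D initiators without prior Drug C, the balancing variable in 7.4.4 and the line variable in Table 9 disagree, so the 2nd/3rd-line subgroups are coded differently by arm. The primary HR shares the problem if the Table 9 variable enters the propensity score.

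The size is illustrative, because neither p nor r is given. At r = 1.5 and p of 10% to 30%, a true HR of 0.90 appears as about 0.93 to 1.01 in the 3rd-line stratum and about 0.92 to 0.96 overall. A reader might take the stratum figures to mean that the planned effect vanishes. That does not carry over: the overall HR is attenuated, and in the range shown it reaches 1.0 only at r = 2 with p = 30%. The bias from this pairing is zero if every Drug D initiator had prior Drug C or if line is not prognostic. It should be corrected before the propensity model is fixed.

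**What to change.** Reconcile section 7.4.4 and Table 9.

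- Derive line by one rule, from history before time 0, in all three groups. The number of prior systemic lines is preferable. Prior Drug C yes/no removes the asymmetry between arms but still miscodes anyone given another second-line drug.
- Use that one variable both for matching and for the subgroups. Match exactly on it, so that subgroup comparisons stay within matched pairs; the 0.2 SD caliper on the propensity score does not ensure this.
- Report how many Drug D initiators have no recorded Drug C, in the concurrent and historical groups. This supplies an upper guide to p, which the documents do not give.
- Add a sensitivity analysis that excludes those patients.

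The cost is rewording one section and one table, deriving prior lines from the registry, and one exact-match term. Some matched pairs may be lost.
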